**Measurement of benefit**

The AQL-8D and EQ-5D-5L will be used to determine HSU for each participant. Mean scores and measures of dispersion will be calculated for both groups. Quality-adjusted life-years (QALYs) will be calculated using two approaches: change from baseline (CfB), and area under the curve (AUC) approach with/without linear regression (49, 50).

#### Uncertainty and sensitivity analysis

A summary measure of the uncertainty of costs and effects will be presented using cost-effectiveness acceptability curves (CEAC). The CEAC will show a range of probabilities of an intervention being cost-effectiveness at different ceiling thresholds (i.e. a maximum amount that decision-makers are willing to pay for a unit of benefit). To test the robustness of the results, a series of sensitivity analyses will be conducted to explore the variability in estimating cost-effectiveness.

$$ICER = \frac{\text{mean cost yoga program group} - \text{mean cost physical therapy group}}{\text{mean QALY yoga program group} - \text{mean QALY physical therapy group}}$$

#### **Timelines:**

| Milestones                                      | 2020 |   |   |   | 2021 |   |   |   | 2022 |   |   |   |
|--------------------------------------------------------|-------------|---|---|---|-------------|---|---|---|-------------|---|---|---|
| Ethics and study set-up                                | X           | X | X | X | X           |   |   |   |             |   |   |   |
| Recruitment, screening, and initiation of intervention |             |   |   |   |             | X | X | X |             |   |   |   |
| 24 weeks visit for final outcomes                      |             |   |   |   |             |   |   |   | X           | X | X |   |
| Data cleaning, analysis and write up                   |             |   |   |   |             |   |   |   |             | X | X | X |

#### **Significance:**

While it is established that the physical component of yoga provides the exercise that is consistent with recommendations for knee OA, the mental component has the potential to increase psychological well-being reducing stress, which can influence the central pain processing and alleviate the pain symptoms. If yoga can improve the pain and function in knee OA, it may slow the progression to joint replacement, thus contributing to cost savings to the health system. The proposed study represents an innovative approach to this and lends itself to easy implementation as yoga is a popular exercise program and can easily be incorporated in the program of management of knee OA.

## **SUMMARY OF PROTOCOL CHANGES**

Protocol Version number 1.6, dated 12 Sep 2022

1. There were no major deviations from the protocol, except for the rescheduling of clinic visits due to COVID-19 restrictions.
2. We acknowledge that additional outcome measures outlined in trial protocol, such as cost-effectiveness (health economics) outcomes, physical activity, gait characteristics, and body fat, are not presented in this manuscript. As the analysis of these data is still ongoing, they have not been included. We remain committed to thoroughly exploring and reporting these outcomes in separate publications.
3. We have collected the serum and urine samples and stored them for analyses. However, we are yet to do the biochemical markers proposed in the protocol and registry due to the lack of funding.

**Study Protocol: A randomised comparative effectiveness trial of YOGa and strengthening exercise for knee osteoArthritis (YOGA Trial)**

**Funding**

This trial is funded by the Rebecca L Cooper Medical Research Foundation.

## STATISTICAL ANALYSIS PLAN (SAP)

There was no separate Statistical analysis plan prepared for this study apart from what was entered into the protocol. These parts of statistical analysis are taken from the protocol, which are available in these documents.

### **SAP as described in the approved version of protocol.**

#### **Statistical consideration**

Hypothesis, primary endpoints (i.e., primary outcome variables), and secondary endpoints

Research hypothesis:

Primary alternative hypothesis: Yoga program will be superior to strengthening exercise program on reducing knee pain (assessed using VAS) over 12 weeks in knee OA patients.

Secondary alternative hypothesis: Yoga program will improve secondary outcomes (namely VAS knee pain over 24 weeks, WOMAC pain, WOMAC function, WOMAC stiffness, OMERACT-OARSI responders, patient global assessment, painDETECT score, Depression (assessed by patient health questionnaire), quality of life (AQoL-8D and EQ-5D-5L), leg muscle strength, core physical performance measures (30-s chair stand test, 40-m fast-paced walk and stair climbs test), and self-reported adherence compared to strengthening exercise.

Primary outcome measure:

Change in overall average knee pain assessed by visual analogue scale (VAS) over 12 weeks.

Pain will be evaluated at each time point using a 100 mm VAS and asked: “On this line, how would you rate your overall average knee pain in the last one week?” For knee pain assessed using VAS, terminal descriptors will be 0 mm = no pain to 100 mm = worst pain possible.

Secondary outcome measures:

1. Change in VAS knee pain over 24 weeks.
2. Change in WOMAC pain, WOMAC function, and WOMAC stiffness over 12 weeks and over 24 weeks.
3. Change in VAS knee pain over 12 weeks in patients with painDETECT > 12
4. Change in core physical performance measures as assessed by 30 s chair stand test, 40 m fast walk test, and stair climb test over 12 and over 24 weeks.
5. Change in Patient Health Questionnaire (PHQ-9) scales over 12 and over 24 weeks.
6. Change in patient global assessment score (assessed using a 100 mm VAS) over 12 and over 24 weeks.
7. Change in neuropathic pain, as assessed by the painDETECT questionnaire, over 12 and over 24 weeks.
8. Change in leg muscle strength will be assessed by leg muscle strength dynamometry at the lower limb (involving both legs simultaneously) over 12 and over 24 weeks.
9. Self-reported adherence to the yoga or strengthening exercise program from baseline to 12 and baseline to 24 weeks will be assessed using an online logbook and defined as the percentage of prescribed sessions undertaken.
10. The OARSI-OMERACT responder criteria: This will be employed to generate a responder categorical variable (0 = non-responder, 1 = responder) based on improvement in WOMAC pain, function, and patient global assessment.
11. Change in QoL (assessed by AQoL-8D and EQ-5D-5L) from baseline to week 12 and baseline to 24 weeks.
12. Change in concomitant pain medications.

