**Primary outcome:**

Change in knee pain assessed by VAS for over 12 weeks. Pain will be evaluated at each time point using a 100mm VAS and asked: “On this line, how would you rate your overall average knee pain in the last one week”? For knee pain assessed using VAS, terminal descriptors will be 0mm = no pain, 100mm = worst pain possible.

**Secondary outcomes:** (overall change from baseline to week 12 and overall change from baseline to week 24 are separate outcomes)

1. Change in VAS knee pain over 12 weeks in patients with painDETECT>12
2. Change in VAS knee pain over 24 weeks.
3. Change in WOMAC knee pain, WOMAC stiffness, and WOMAC knee function over 12 weeks and over 24 weeks.
4. Change in physical function as assessed by 30s Chair Stand Test, 40m Fast Walk Test and Stair Climb Test over 12 and over 24 weeks
5. OMERACT\_OARSI responders (meeting responder criteria) at week 12, and 24 weeks
6. Change in biomarker (urinary CTX-II, serum COMP, and serum hyaluronan) and systemic inflammatory markers (hs-CRP, IL-6, TNF- $\alpha$ ) over 12, and over 24 weeks
7. Change in Patient Health Questionnaire (PHQ-9) scales over 12, and over 24 weeks
8. Change in patient global satisfaction score over 12, and over 24 weeks
9. Change in painDETECT scores over 12, and over 24 weeks
10. Change in leg muscle strength (quadriceps) over 12, and over 24 weeks
11. Change in gait speed from baseline to week 12 and baseline to 24 weeks

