**Data analysis:**

The comparisons of pain and other continuous outcomes will be done employing a repeated measures mixed model incorporating terms of treatment, time, and respective baseline values as covariates. We will also assess the effects of potential confounders or interaction with treatment by covariates, including age, sex, BMI, disease severity, comorbidities, health status, and use of pain medications. A two-sided p-value less than 0.05 will be considered to indicate the statistical significance, and the results will be shown as the between-group differences with 95% confidence intervals (95% CIs) of the differences.

We will explore the role of clustering effects in the trial by performing a sensitivity analysis examining the implications of clustering by the instructor by adding an instructor random effect to our mixed-effects model.

We will also perform an exploratory analysis to investigate whether the presence or absence of neuropathic pain, as assessed by the painDETECT questionnaire, is a potential moderator that influences response to treatment for the primary outcome at 12 weeks. To assess the moderation of the effect by painDETECT (binary moderator), an interaction term between the randomised group and the potential moderator will be included in outcome regression models.

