3. **Original Protocol:** We stated “the above sample size will allow us to detect a non-inferiority of yoga with strengthening exercise. Non-inferiority would be declared if the mean change in knee pain (assessed using VAS) in the yoga group was not significantly worse than the mean change in the strengthening exercise group, within a pre-stated margin of non-inferiority ( $\Delta$ ), in this case, set at 10 mm”.

**Open access protocol publication:** We stated “the above sample size will allow us to detect a non-inferiority of yoga with strengthening exercise. Non-inferiority would be declared if the mean change in knee pain (assessed using VAS) in the yoga group was not significantly worse than the mean change in the strengthening exercise group, within a pre-stated margin of non-inferiority ( $\Delta$ ), in this case, set at 10 mm”.

**Final Manuscript:** Since our study was powered for non-inferiority and has met the criteria for switching the trial objective from superiority to non-inferiority, as outlined by the European Agency for the Evaluation of Medicinal Products (EMA 2001), we conducted a non-inferiority analysis.

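### The SAP hypothesises superiority of yoga on about 29 secondary outcome-by-time tests, each at two-sided 0.05, with no gate, order, error control or exploratory label

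*Combined protocol and SAP*

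**What the plan says.** The SAP (*Statistical consideration*, Research hypothesis) sets out a formal alternative hypothesis for the secondary outcomes, separate from the primary one: "Secondary alternative hypothesis: Yoga program will improve secondary outcomes (namely VAS knee pain over 24 weeks, WOMAC pain". The sentence goes on to name function, stiffness, responders, global assessment, painDETECT, depression, quality of life, leg strength, the performance tests and adherence, all in comparison with strengthening exercise.

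The protocol's heading for the secondary outcomes adds that "overall change from baseline to week 12 and overall change from baseline to week 24 are separate outcomes". The SAP's numbered list follows suit, for example "Change in WOMAC pain, WOMAC function, and WOMAC stiffness over 12 weeks and over 24 weeks".

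One decision rule covers everything. SAP *Data analysis* says "A two-sided p-value less than 0.05 will be considered to indicate the statistical significance". The protocol's *Statistical Analyses* section and the section on the analysis used in the final manuscript set the same two-sided 0.05 level.

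The documents state that no SAP exists beyond the protocol text, so they point to no multiplicity plan held elsewhere. The word exploratory appears in the SAP only for the painDETECT moderator analysis.

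**The concern.** A trial with one named primary outcome may reasonably leave its secondary outcomes unadjusted if it treats them as supportive or exploratory. This plan does something else. It hypothesises that yoga is better on each of them and calls any result below 0.05 significant. Under that rule a single nominally significant result among many can be presented as demonstrated superiority, and the reader has no stated error rate against which to judge it.

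The change log makes this more relevant. It says the study "has met the criteria for switching the trial objective from superiority to non-inferiority" and that a non-inferiority analysis was carried out. No passage then says what status the secondary superiority hypothesis has when primary superiority is not shown.

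**Working it through.** **The plan's own figure.** The documents give no family-wise error rate for the secondary outcomes. The only stated error and power figures are for VAS pain: difference 15 mm, SD 22.5, two-sided 0.05, 90% power. Per arm, 2 × (1.960 + 1.282)² × 22.5² / 15² = 47.3, so 48 per arm by the normal approximation. The t-test version gives 48.26, so 49 per arm and 98 in total, as stated. The design calculation is thus for one comparison at 0.05.

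**Count of tests in the hypothesis sentence**, with time points from the protocol's and SAP's secondary outcome lists:

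- VAS pain ("Change in VAS knee pain over 24 weeks"; the 12-week change is primary): 1
- WOMAC pain, function and stiffness, two times: 6
- Performance tests ("30 s chair stand test, 40 m fast walk test, and stair climb test over 12 and over 24 weeks"): 6
- AQoL-8D and EQ-5D-5L, two times: 4
- Responders, patient global assessment, painDETECT, PHQ-9 ("Change in Patient Health Questionnaire (PHQ-9) scales over 12 and over 24 weeks"), leg strength and adherence, two times each: 6 × 2 = 12

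Total: 1 + 6 + 6 + 4 + 12 = 29.

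**Independent tests, no true effect on any.** A two-sided 0.05 test has a 0.025 chance of a false result favouring yoga.

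- At least one favouring yoga: 1 − 0.975^29 = 0.520
- At least one in either direction: 1 − 0.95^29 = 0.774
- Expected false positives: 29 × 0.05 = 1.45, of which 29 × 0.025 = 0.725 favour yoga

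**Correlated tests.** Independence is not credible here. The same participants are measured at both times, the WOMAC subscales and the two quality-of-life instruments overlap, and the responder variable is built from three other listed outcomes. The documents give no correlations, so a range was simulated (29 normal test statistics, equal correlation, 400,000 draws):

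| Assumed correlation | At least one favouring yoga | At least one, either direction |
|---|---|---|
| 0 | 52% | 77% |
| 0.2 | 40% | 71% |
| 0.3 | 34% | 65% |
| 0.5 | 25% | 50% |
| 0.7 | 17% | 33% |
| 0.8 | 13% | 25% |

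A structured version, with correlation 0.2 to 0.5 between outcomes and 0.6 to 0.7 between times, gives about 27% to 40% favouring yoga.

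**Sensitivity to the count, under independence, favouring yoga.** Leaving out adherence (27 tests) gives 50%. Adding the painDETECT > 12 subgroup, which is listed as a secondary outcome but is not in the hypothesis sentence (30 tests), gives 53%. Adding concomitant medication at two times as well (32 tests) gives 56%. The result does not turn on the exact count.

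**The case against.** Several points on the other side have force.

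- One primary outcome is named, only it is powered, and the full secondary list is disclosed. Many trials leave secondary outcomes unadjusted. That is fair, but such practice relies on treating them as exploratory, and this plan states a superiority hypothesis instead.
- The plan already asks for differences between arms with 95% CIs, which is a main part of good reporting. What is missing is the statement that they are unadjusted, and restraint in wording.
- The rates assume no true effect on any of the 29 tests, and correlations that the documents do not supply. This stands, and is why a range is given.
- Adherence is a process measure, and the methods-used section lists no model for it. This stands, but dropping it changes little.

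Three stronger readings are tempting. First, a reader might infer that a false claim in favour of yoga has roughly an even chance. At a correlation of 0.5 the 50% counts results in either direction, including those favouring strengthening exercise; the yoga-favouring figure there is 25%, and about 50% requires independence. Second, a reader might infer that secondary results were in fact presented as confirmed superiority. The documents do not show this, and the manuscript is not among them. Third, a reader might infer that moving to non-inferiority removed a gate. The plan never had one: the gap is already in the hypothesis and the significance rule.

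**Conclusion.** The point holds as a gap in how secondary superiority claims are controlled and labelled. It is more than missing detail, because the stated rule itself inflates false claims of superiority. If yoga had no true effect on any of the 29 tests, the chance of at least one false significant result in its favour is 52% under independence, about 25% to 40% at assumed correlations of 0.5 to 0.2, and about 13% at 0.8. Against the nominal 2.5%, even the last is about five times too high (13 / 2.5 = 5.2). The conclusion and the remedy are the same at every value in that range. The primary comparison is not affected.

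**What to change.** In SAP *Statistical consideration* and *Data analysis*, and in the reporting described under the final-manuscript analysis and the change log:

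- State that superiority on secondary outcomes is not claimed as confirmatory unless superiority on the primary outcome is shown.
- Report all secondary outcomes as exploratory: estimated differences between arms with 95% CIs, described as unadjusted for multiplicity, without calling any of them significant or superior.

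Do not add a fixed-sequence list now. The documents describe completed analyses, so an order chosen at this stage could not provide confirmatory error control.

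The cost is wording only; no new data or re-analysis is needed. The downside is that nominally significant secondary results can no longer be presented as confirmed.

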### **Treatments:**

Overall, 126 eligible participants will be randomly allocated to a 24-week group-based *yoga program* or *strengthening exercise program* (each with two 1-hour group-based sessions and one 1 hour home based session per week). Group sessions will be led by physiotherapist/exercise physiologists/yoga teachers for the first 12 weeks. Trainers will lead a group of approximately 10 participants. Participants will be instructed to continue their *yoga* or *strengthening exercise* at home for another 12 weeks. Using REDCap, weekly email follow-up will be done with the participants to confirm the compliance to the home-based program, and video instructions will be given to each participant to support the home-based program.

An evidence-based *yoga program* designed by a yoga expert and researcher - [name] from the Maryland University of Integrative Health, USA will be delivered by yoga

teachers. Each yoga class will begin with a breathing exercise (*pranayama*) and chanting (10min), warm-up, and moving sequences (*asanas*, 40 min). Classes will end with deep relaxation (*savasana*) and meditation (10 min). Classes will include an application of yoga philosophy and replace negative thoughts with positive ones (*pratipaksa bhavanam*). Details about interventions are in the appendix.

The strengthening exercise therapy regimen will be designed by [name] as a group-based progressive strengthening exercise program based on those used in past clinical trials and shown to be effective. Details about interventions are in the appendix.

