The teachers leading the yoga/strengthening exercise classes will ensure the exercises are performed safely. It is usual to feel some pain/discomfort in the knee during the exercise but the amount of pain will be monitored. When levels of pain are deemed unacceptable by the participant and/or teacher, the exercise program will be modified accordingly. Participants will use similar principles in the unsupervised home sessions. In particular, they will be advised that if the pain has not subsided to usual levels by the next day or there has been increased night pain or swelling in the knee, the exercise program should be modified by reducing the

intensity or frequency of the exercises or by leaving out one or more exercises that may be contributing to the increase in symptoms.

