**Health Economics Outcomes (secondary outcomes):**

We will assess health state utility (HSU) values, resource utilisation, and costs throughout the study. Health-related quality of life (HRQoL) and utility will be assessed using the Assessment of Quality of Life (AQoL-8D) and the EuroQol 5 dimensions (EQ-5D-5L) instruments. The health economic outcomes to be collected as the secondary outcome will include:

12. Change in concomitant medications (assessed using self-reported medication history questionnaire) from baseline to 12 and baseline to 24 weeks and associated costs.

13. Self-reported adherence to the intervention and comparator program from baseline to 12 and baseline to 24 weeks assessed using online logbook and defined as the percentage of prescribed session undertaken.
14. Change in QoL (assessed by AQoL-8D and EQ-5D-5L) from baseline to week 12 and baseline to 24 weeks.
15. Change in health resource utilisation (assessed using a self-reported questionnaire) at 12 and 24 weeks.

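### Adherence is a hypothesised between-arm outcome but rests wholly on self-report, although most sessions in weeks 1–12 are trainer-led classes; it also counts sessions, not dose

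*Combined protocol and SAP*

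**What the plan says.** The SAP section on statistical considerations lists, as secondary outcome 9, "Self-reported adherence to the yoga or strengthening exercise program from baseline to 12 and baseline to 24 weeks", which "will be assessed using an online logbook and defined as the percentage of prescribed sessions undertaken". The protocol's health economics outcomes (item 13) give the same measure: "Self-reported adherence to the intervention and comparator program", "defined as the percentage of prescribed session undertaken". The SAP's secondary alternative hypothesis includes adherence among the outcomes expected to favour yoga. The protocol's cost-effectiveness section also plans a subgroup analysis by adherence to the yoga program.

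The Treatments section sets the schedule: "each with two 1-hour group-based sessions and one 1 hour home based session per week". Trainers lead groups of about 10 for the first 12 weeks, after which participants continue "at home for another 12 weeks". A weekly REDCap email asks about compliance with the home program.

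The Safety section covers modification for pain. In classes: "When levels of pain are deemed unacceptable by the participant and/or teacher, the exercise program will be modified accordingly"; no route is named. In unsupervised home sessions, participants whose pain does not settle, or who have more night pain or swelling, are advised to modify by lowering "intensity or frequency of the exercises or by leaving out one or more exercises that may be contributing to the increase in symptoms".

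**The concern.** There are two separate weaknesses.

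**Source.** Participants cannot be unaware of whether they do yoga or strengthening, and they supply all the adherence data. If enthusiasm for the assigned program affects how fully the logbook is completed, the comparison between arms is biased. A trainer is present at every class and could record attendance, but no such register is named as a source.

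**Meaning.** A session done lightly, or with exercises left out, appears to count the same as a full one. A session dropped for the same reason counts as missed. The text does not say whether a modified session counts as undertaken, or whether the denominator is the original or the modified program.

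At stake are the adherence comparison itself, the planned cost-effectiveness subgroup, and any use of the score to describe how much exercise each arm received.

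**Working it through.** The documents give no adherence figure, threshold or power calculation, so there is no stated number to reproduce. What follows is session arithmetic.

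**Step 1: how much of the score could be observed.** Inputs from the Treatments section: 2 class sessions and 1 home session per week, classes led for 12 weeks.

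- Prescribed in weeks 1–12: (2 + 1) × 12 = 36.
- Classes: 2 × 12 = 24, and 24/36 = 66.7% of the 12-week denominator.
- If three sessions a week continue at home in weeks 13–24 (an assumption, because the frequency for that phase is not clearly restated), the 24-week denominator is 72. Classes are then 24/72 = 33.3% and home sessions 48/72 = 66.7%.

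**Step 2: what a class attendance error costs.** Each class wrongly logged as attended moves the 12-week score by 1/36 = 2.8 points. The documents give no error rate, so as a range:

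- a net between-arm difference of 1 class per person shifts the comparison by 2.8 points;
- 2 classes, by 2/36 = 5.6 points;
- 4 classes, by 4/36 = 11.1 points.

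Equal over-reporting in both arms cancels. A register would remove this source of error for the 24 classes.

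**Step 3: what the score registers when a program is modified.** Score = sessions undertaken / sessions prescribed.

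| Pattern | Score |
|---|---|
| All 36 sessions done, each lightened by a third | 36/36 = 100% |
| One session a week missed for 12 weeks, original denominator | 24/36 = 66.7% |
| Same, denominator reset to the modified program | 24/24 = 100% |
| One session missed in 4 of the 12 weeks | 32/36 = 88.9% |
| Every home session halved, weeks 1–12 | 36/36 = 100% |
| Alternate home sessions skipped, weeks 1–12 | 30/36 = 83.3% |
| One session a week missed for 24 weeks (72 prescribed) | 48/72 = 66.7% |
| One session a week missed for 12 of the 24 weeks | 60/72 = 83.3% |

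Only missed sessions move the score, and the reset-denominator row shows that even those may not. In weeks 1–12 there is one home session a week. Reaching 66.7% by the home-session advice alone therefore means giving up all 12 of them.

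**Step 4: would counting only sessions completed as prescribed measure dose better?** No. A participant who lightens all 36 sessions would score 0/36 = 0%, and one who drops a session a week would score 24/36 = 66.7%. The distortion is larger and reversed.

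**The case against.** The percentage of sessions done is a clear, pre-specified attendance measure, stated consistently in the protocol and the SAP, and neither calls it a measure of dose. Adjusting the program to the participant is part of both interventions, so someone who attends and modifies as advised is reasonably called adherent. The three named routes belong to the home-session advice, which is triggered by symptoms and may apply only for short spells. The same rules govern both arms. The intervention appendix and the logbook fields are not in the supplied text, so class attendance or modifications may be recorded somewhere.

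Most of this stands. It rules out saying that delivered dose cannot be compared at all: session counts remain comparable, and unseen records may hold more. It also answers a reader who might infer that the non-inferiority conclusion fails without dose data. Non-inferiority is judged on VAS pain against the 10 mm margin, and adherence does not enter that criterion. Leg strength and physical performance tests are also planned, with assessors blinded for objective measures, and they bear on whether the comparator worked.

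What it does not answer is the source. For an outcome hypothesised to differ between arms, the stated measure relies on reports from unblinded participants even for sessions that a trainer watches.

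**Conclusion.** The point holds as a cheap improvement to one secondary outcome. As described, adherence is wholly self-reported, although 24 of the 36 sessions in the 12-week score are directly observable. It counts sessions, so it should not be presented as delivered dose, and its denominator after a modification is undefined.

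A reader might go further and take 100% versus 67% for the same dose cut as a property of the plan. That needs three assumptions the documents do not make: that a one-third cut in intensity equals one missed session in dose, that the cut lasts the whole period, and that the denominator stays at three a week.

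A reader might also infer a spurious gap of 0.30 × (100 − 66.7) = 10.0 points between arms. This further assumes that 30% of each arm modify, all through intensity in one arm and all through frequency in the other. Nothing in the documents suggests that the arms differ in route; with the same pattern of modification in both, this gap is zero. The size of any reporting bias is likewise unknown, and the figures in step 2 are a range under assumption. The primary analysis and the sample size are untouched.

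**What to change.** 1. Take class attendance, in person or by Zoom, from a register kept by the trainer. Use the online logbook for home sessions only.
2. State that the denominator is the number of sessions originally prescribed, whatever is later modified. State the weekly number that applies in weeks 13–24, and say that a modified session counts as undertaken.
3. Add one item to the weekly log: whether any session was modified and by which route (intensity, frequency, exercises omitted). Report the frequency of modification by arm beside the session percentage, as description. Item 2 alone does not turn the score into a dose measure, so this item is needed to interpret it.
4. Do not adopt sessions completed as prescribed as the measure of dose, for the reason in step 4. Leave the Safety section's modification rules as they are.

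The cost is one register per class, kept by staff already present, and one extra weekly question. Data entry rises slightly, and reported adherence may be lower. Where collection has already finished, the denominator rule and a statement that the score measures sessions rather than dose can still be added, and any existing class records can be used.
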